## Abstract

**Background:**

Standard treatment for drug-susceptible tuberculosis (DS-TB) includes a multidrug regimen requiring at least 6 months of treatment, and this lengthy treatment easily leads to poor adherence. There is an urgent need to simplify and shorten treatment regimens to reduce interruption and adverse event rates, improve compliance, and reduce costs.

**Methods:**

ORIENT is a multicenter, randomized controlled, open-label, phase II/III, non-inferiority trial involving DS-TB patients to evaluate the safety and efficacy of short-term regimens compared with the standardized six-month treatment regimen. In stage 1, corresponding to a phase II trial, a total of 400 patients are randomly divided into four arms, stratified by site and the presence of lung cavitation. Investigational arms include 3 short-term regimens with rifapentine 10 mg/kg, 15 mg/kg, and 20 mg/kg, while the control arm uses the standardized six-month treatment regimen. A combination of rifapentine, isoniazid, pyrazinamide, and moxifloxacin is administered for 17 or 26 weeks in rifapentine arms, while a 26-week regimen containing rifampicin, isoniazid, pyrazinamide, and ethambutol is applied in the control arm. After the safety and preliminary effectiveness analysis of patients in stage 1, the control arm and the investigational arm meeting the conditions will enter into stage 2, which is equivalent to a phase III trial and will be expanded to recruit DS-TB patients. If all investigational arms do not meet the safety conditions, stage 2 will be canceled. In stage 1, the primary safety endpoint is permanent regimen discontinuation at 8 weeks after the first dose. The primary efficacy endpoint is the proportion of favorable outcomes at 78 weeks after the first dose for both two stages.

**Discussion:**

This trial will contribute to the optimal dose of rifapentine in the Chinese population and suggest the feasibility of the short-course treatment regimen containing high-dose rifapentine and moxifloxacin for DS-TB.

**Trial registration:**

The trial has been registered on ClinicalTrials.gov on 28 May 2022 with the identifier NCT05401071.

**Supplementary Information:**

The online version contains supplementary material available at 10.1186/s12879-023-08264-2.

## Background

Tuberculosis (TB) is one of the most important global healthcare challenges, and is one of the leading causes of death from infectious pathogens, with 10.6 million people contracting TB and 1.6 million dying from it in 2021 [1]. Currently, the course of chemotherapy for the initial treatment of drug-susceptible tuberculosis (DS-TB) is 6 months, which is much longer than that of other respiratory diseases [2]. Minimal non-adherence to TB treatment was associated with an increased risk for unfavorable outcomes [3]. The development of new and safe therapeutic strategies with potent bactericidal activity is the main approach to short treatment duration, improve compliance and ensure the success rate, thus reducing the burden of both doctors and patients [4].

On the strength of their powerful bactericidal and sterilizing activities, rifamycins are the cornerstone of modern chemotherapy for active TB with a 6-month course and play a vital role in preventing recurrence after cessation of treatment [5]. Rifampicin and rifapentine are the two forms of rifamycins. Rifampicin is the most commonly used rifamycin in the treatment of TB. The association between rifampicin exposure and antimicrobial activity was confirmed in previous phase I and II clinical trials, as assessed by early bactericidal activity and sputum culture conversion time, and the plateau of rifampicin activity was not achieved even at doses as high as 35 mg/kg/d [6–8]. As the cyclopentyl derivative of rifampicin, rifapentine has a longer half-life and a lower minimum inhibitory concentration than rifampicin [9, 10]. Therefore, the potential of rifapentine in intensifying treatment was explored [11–13]. The use of higher and more frequent doses of rifapentine was shown to achieve higher cure rates with a satisfactory safety profile, even at doses up to 20 mg/kg/day [14–18].

Apart from high-dose rifapentine, using fluoroquinolones in constructing a new regimen is thought to probably contribute to shortening the treatment duration of DS-TB [19]. However, it is worth noting that compared with the standard treatment, 4-month fluoroquinolone-contained regimens were shown inferior in three large trials in 2014 [20–22], which implied fluoroquinolones alone were not sufficient to shorten the course of treatment [23]. An animal study conducted in 2007 showed that combined treatment with rifapentine and moxifloxacin showed high early bactericidal activity in a mouse model of TB and provided a high cure rate after 3 months of treatment [24].

Since then, the combination of fluoroquinolones and higher doses of rifapentine has received considerable attention. The results of a multicenter randomized controlled trial S31/A5349, published in the New England Journal of Medicine in April 2021, showed that replacing rifampicin with a high dose of rifapentine (1200 mg daily) and substituting moxifloxacin for ethambutol could shorten the treatment period of DS-TB to 4 months without increasing the occurrence of adverse events (AEs). This strategy proved to be non-inferior to the standard regimen and was recommended by the World Health Organization (WHO) in May 2022 [2, 25].

Enthusiasm over the promising four-month regimen based on high-dose rifapentine and moxifloxacin has been curtailed following clinicians’ concerns about potential hepatotoxicity as the dose of rifapentine in the recommended regimen is much higher than that approved by the US Food and Drug Administration (FDA) and the China National Medical Product Administration (NMPA). Therefore, it is imperative to continuously evaluate the safety profile and efficacy of the high-dose rifapentine-based regimen among expanded populations and explore the possibility and practicability of optimizing the dose of rifapentine without compromising efficacy.

To delight this uncertain, we propose a phase II/III, multicenter, open-label, noninferiority, randomized clinical trial, entitled “Optimizing RIfapentine-based regimen and shortENing the treatment of Tuberculosis research (ORIENT)”, aiming to evaluate whether the 4-month regimen containing high-dose rifapentine and moxifloxacin is as effective and safe as the 6-month standard regimen for DS-TB in Chinese people.

The effectiveness, safety, and tolerability of a new four-drug therapy for 17 weeks will be explored in comparison with the standard 6-month treatment for DS-TB. At the same time, considering some characteristics that may have an impact on drug efficacy, the pharmacokinetic/pharmacodynamic (PK/PD) analysis of rifapentine and its desacetyl metabolite and moxifloxacin will be performed. And the protocol of this clinical trial is presented here.

## Method

### Study objectives

ORIENT is a phase II/III, multicenter, open-label, randomized controlled clinical trial of non-inferiority design, recruiting DS-TB patients susceptible to rifampicin, isoniazid, pyrazinamide, ethambutol, and fluoroquinolones. The purpose of this study is to a) Evaluate the safety, tolerability, and PK/PD of a high-dose rifapentine regimen; b) Evaluate whether the regimen containing high-dose rifapentine and moxifloxacin may reduce the duration of DS-TB treatment to 17 weeks; c) define the optimal dose of rifapentine in the Chinese population.

### Study design

The study is composed of two stages in a seamless progression, which means only after the decision has been taken following the analysis of stage 1 primary endpoint, the participant recruitment of stage 2 will start. Figure 1 shows the flowchart of ORIENT trial. The WHO standardized regimen for DS-TB is used as a control arm for two stages.

**Fig. 1 Fig1:**
[figure not shown]
ORIENT study schematic. The trial plans to recruit DS-TB patients susceptible to rifampicin, isoniazid, pyrazinamide, ethambutol, and fluoroquinolones. Participants will be randomly divided into different arms as shown in the figure. Abbreviations in this figure: DS-TB: drug-susceptible tuberculosis. 8wHRZE/18wHR: rifampicin (R), isoniazid (H), pyrazinamide (Z), and ethambutol (E) for 8-week intensive phase and rifampicin and isoniazid for 18-week continuous phase. 8wHPZM/9wHPM: rifapentine (P), isoniazid(H), pyrazinamide (Z), and moxifloxacin (M) for 8-week intensive phase and rifapentine, isoniazid and moxifloxacin for 9-week continuous phase. 8wHPZM/18wHPM: rifapentine (P), isoniazid (H), pyrazinamide (Z), and moxifloxacin (M) for 8-week intensive phase and rifapentine, isoniazid and moxifloxacin for 18-week continuous phase

Stage 1 corresponds to the phase II trial, aiming to evaluate the safety of investigational regimens in patients with DS-TB. Recruited participants are randomly assigned to the Short Regimen with Rifapentine 10 mg/kg, Short Regimen with Rifapentine 15 mg/kg, and Short Regimen with Rifapentine 20 mg/kg as investigational arms and the WHO Standardized Regimen as a control arm.

If at least two investigational arms meet the safety conditions in the stage 1 analysis, the two investigational arms with the higher conversion rate of liquid culture in 8 weeks and the control arm will enter stage 2. The subsequently enrolled patients will be expanded and be allocated to the 3 arms at a random ratio of 1:1:1. If only one arm meets the safety conditions in stage 1, the participants with DS-TB will be expanded and be 1:1 randomly assigned to this certain investigational arm and the control arm. If all investigational arms in stage 1 fail to meet the safety conditions, stage 2 will be canceled.

### Study regimens and comparator

The rifapentine regimens are composed of two periods of 17 to 26 weeks. The first phase is an 8-week intensive phase, including rifapentine (P), isoniazid (H), pyrazinamide (Z), and moxifloxacin (M) for daily use. This is followed by a 9-week continuation phase with the following agents every day: rifapentine, isoniazid, and moxifloxacin (8wHPZM/9wHPM) (The continuation phase should be extended to maximum of 18 weeks for patients who have lung cavitation at the end of 17 weeks treatment on chest radiography or positive sputum culture in liquid medium at the end of 8 weeks treatment (8wHPZM/18wHPM)). The control regimen is the WHO standardized regimen with two phases of treatment for 26 weeks. The first is an intensive phase using rifampicin, isoniazid, pyrazinamide, and ethambutol (E) every day for 8 weeks. This is followed by a continuation phase of 18 weeks with the following agents for daily use: rifampicin and isoniazid (8wHRZE/18wHR). Table 1 shows the doses and usage of each drug in the WHO standardized regimen and the short regimen with rifapentine.

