	3) Participants die during treatment (excluding force majeure factors such as homicide, traffic accidents or natural disasters); death associated with tuberculosis during follow-up (after completion of study treatment)
	4) Withdrawal from the trial or loss to follow-up during treatment (except pregnancy, accident, etc.)
	5) Participants stop the initial treatment, and restart different tuberculosis treatments
	6) Restart tuberculosis treatment after the end of expected treatment
	7) The treatment course exceeds the expected treatment length by more than 2 weeks regardless of any reason
	8) The treatment regimen is changed (including dosage or frequency of administration) except for pregnancy, exogenous reinfection, and rechallenge
Not assessable	The outcome will be classified as not assessable if not classified as unfavorable and meets any one of the following criteria: 1) Loss to follow-up (after completion of study treatment) with the last sputum culture being negative; 2) Sputum cannot be produced or is contaminated at the end of follow-up period, but stable culture conversion has not been achieved before and the last sputum culture is negative; 3) Alteration of treatment due to pregnancy; 4) Death unrelated to tuberculosis during follow-up (after completion of study treatment); 5) Death due to force majeure such as homicide, car accident or natural disaster during treatment; 6) Extension or change of tuberculosis treatment after the whole genome sequencing confirms exogenous reinfection

^a^Stable culture conversion is defined that the subject shows negative culture of *M. tuberculosis* in two consecutive samples (at least 2 weeks apart) for the first time, and subsequently no positive culture of *M. tuberculosis* or only one single positive (at least two consecutive bacterial cultures after the definition of the positive strain are negative, and no evidence of exogenous reinfection is found after sequencing of the positive strain) is shown

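### The stage 2 test compares a response-guided 17 to 26 week rifapentine strategy with 26 weeks of control, so it cannot answer the stated 17-week question

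*Protocol article*

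**What the plan says.** Three places in the protocol article pose a fixed-duration question. Study objectives, item b, asks whether the regimen "may reduce the duration of DS-TB treatment to 17 weeks". The Background describes the trial as "aiming to evaluate whether the 4-month regimen containing high-dose rifapentine and moxifloxacin is as effective and safe as the 6-month standard regimen", and adds that "a new four-drug therapy for 17 weeks will be explored in comparison with the standard 6-month treatment".

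Study regimens and comparator describes something wider: "The rifapentine regimens are composed of two periods of 17 to 26 weeks". There are two triggers for the longer course. One is radiographic: "The continuation phase should be extended to maximum of 18 weeks for patients who have lung cavitation at the end of 17 weeks treatment". The other is bacteriological: "positive sputum culture in liquid medium at the end of 8 weeks treatment (8wHPZM/18wHPM". For control, "The control regimen is the WHO standardized regimen with two phases of treatment for 26 weeks". The extension rule applies to the rifapentine arms only.

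Assessment and analysis of outcome declares non-inferiority when the upper 95% confidence bound for control minus rifapentine, in the mITT population, is below 6.6 points. It makes no distinction by duration received. Item 7 of the unfavorable outcomes in Table 3 reads: "The treatment course exceeds the expected treatment length by more than 2 weeks regardless of any reason". The article does not define the expected length for a patient who has been extended.

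**The concern.** The stated question and the tested comparison differ. Patients whose week-8 culture or week-17 radiograph meets a trigger may be treated for as long as control patients, and their outcomes count in the rifapentine arm. A non-inferior result would show that starting on rifapentine and deciding the length by response is acceptable. It would not show that 17 weeks is acceptable for everyone randomised, which is how objective b and the aims read.

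A secondary problem concerns the endpoint. A full extension adds 9 weeks (26 − 17), well beyond the 2-week tolerance in item 7, and that item allows no exception for cause. Whether an extension made under the protocol counts as failure is left to the reader.

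**Working it through.** **Step 1: the plan's own figures.** Inputs from Sample size assumptions: control 85.4%, test 84.5%, margin 6.6 points, power 80%, α = 0.025 (three arms) or 0.05 (two arms). These match one-sided levels in n = (z₁₋α + z₀.₈)² × [0.854 × 0.146 + 0.845 × 0.155] / (0.066 − 0.009)².

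- α = 0.025: 7.849 × 0.25566 / 0.003249 = 617.6, so 618.
- α = 0.05: 6.183 × 0.25566 / 0.003249 = 486.5, so 487.
- Losses of 12% + 12%: 618 / 0.76 = 813.2, so 814; 487 / 0.76 = 640.8, so 641.

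All four figures reproduce. They use one success rate for the whole test arm, so they size the whole-arm comparison.

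**Step 2: durations.** Rifapentine without extension is 8 + 9 = 17 weeks. Rifapentine fully extended is 8 + 18 = 26 weeks. Control is 8 + 18 = 26 weeks. The rifapentine arm therefore mixes 17-week courses with courses of up to the control's length, in a proportion the article does not give.

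**Step 3: what an arm-level deficit can mean for 17-week patients.** Let f be the share extended, d_ext the deficit of extended patients against comparable controls, and d₁₇ the same for patients who stop at 17 weeks. Then:

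arm-level deficit = (1 − f) × d₁₇ + f × d_ext

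Setting the left side to 6.6 gives d₁₇ = (6.6 − f × d_ext) / (1 − f). Both f and d_ext are my assumptions:

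| f | d_ext = −5 | d_ext = 0 | d_ext = 6.6 | d_ext = 10 |
|---|---|---|---|---|
| 10% | 7.9 | 7.3 | 6.6 | 6.2 |
| 20% | 9.5 | 8.3 | 6.6 | 5.8 |
| 40% | 14.3 | 11.0 | 6.6 | 4.3 |

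For example, with f = 20% and d_ext = 0, 6.6 / 0.8 = 8.25. With d_ext = 10, (6.6 − 2.0) / 0.8 = 5.75. The whole-arm result does not bound the 17-week deficit in either direction. The comparable controls are also a notional group, because the triggers depend on response to the treatment received.

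**Step 4: item 7 under its two readings.** If the expected length of an extended patient is the extended length, extension alone makes nobody unfavorable. If it is 17 weeks, every fully extended patient is unfavorable. On that second reading, suppose extended patients would otherwise succeed at the planned 84.5%. The planned deficit of 85.4 − 84.5 = 0.9 points then reaches 6.6 once f × 84.5 = 5.7, that is f = 5.7 / 84.5 = 6.7%. The second reading is strained, but the endpoint is sensitive to which one is meant.

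**The case against.** The strongest reply is that the strategy is open and intended. The Abstract gives 17 or 26 weeks for the rifapentine arms, Figure 1's legend lists the extended regimen, and the Discussion says duration is individualised by response. The non-inferiority rule speaks of the rifapentine regimen without naming 17 weeks, and the closing paragraph promises only a shorter duration. All of this is true. It shows that nothing is hidden and that the trial can support a strategy claim. It does not bring objective b and the Background aims into line with that claim.

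Several stronger readings are tempting and are not supported:

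- A reader might infer that the primary test is invalid. It is not: it compares arms as randomised, and its size reproduces.
- A reader might infer a definite dilution of the margin. No extended share is given, and the direction depends on how extended patients fare.
- A reader might infer that the patients most likely to relapse never test the short course. The article does not establish this; its own limitations say that the 8-week outcome may be unrelated to relapse.
- A reader might infer that, if 26 weeks is the expected length, no extended patient can fail item 7. A course running more than 2 weeks past 26 still would, and the other unfavorable criteria still apply.
- A reader might infer that no analysis by duration is planned. The SAP and full protocol are not shown, so this cannot be said.

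On item 7, the objection that a protocol-directed extension is naturally an expected one is fair. What remains is a call for explicit wording.

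**Conclusion.** The point holds as a mismatch between the question stated and the comparison tested. A declared non-inferiority in stage 2 would support a response-guided 17 to 26 week strategy against 26 weeks, and not a fixed 17-week regimen. Its numerical size cannot be fixed from the article. The values of 8.3 points (20% extended) and 11.0 points (40%) hold only with an assumed share and no deficit in extended patients.

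Item 7 and the extension rule need reconciling because the primary endpoint rests on them, although the natural reading is that a protocol-directed extension is not unfavorable. No view is taken on which treatment length or extension rule is right.

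**What to change.** 1. Reword objective b, the two Background aims and the conclusion to be drawn from stage 2, so that each refers to a response-guided 17 to 26 week rifapentine strategy compared with 26 weeks of the standard regimen.
2. Report with the primary result the proportion in each rifapentine arm that finishes at 17 weeks, so that readers can see how far the strategy shortened treatment.
3. Reconcile item 7 of the unfavorable outcomes with Study regimens and comparator, and state explicitly whether an extension made under the protocol counts as unfavorable.
4. Label any comparison limited to patients who were not extended as descriptive. Week-8 culture and week-17 cavitation arise after randomisation and can be affected by treatment, so applying the same criteria to control does not restore a randomised comparison. It must not become the route to a 17-week claim.

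The cost is wording and one descriptive proportion. Sample size, margin and extension rule stay as they are. The downside is a narrower headline claim.

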**Table 1 Tab1:**
[figure not shown]
Doses and usage of study drugs by body weight

All drugs will be administered orally

Rifampicin, isoniazid and pyrazinamide are given once a day before breakfast

Moxifloxacin and rifapentine should be administered together once daily with food

Ethambutol should be taken by body weight 750 to 1000 mg/d, divided into 1 to 3 times, before or after meals

### Enrollment termination criteria and safety conditions in stage 1 analysis

The primary aim of stage 1 is to choose drug regimens for the assessment of stage 2, based on the 8-week efficacy and safety endpoint evaluation. Any study arm will be terminated early when any of the following conditions are present: 1) The number of patients with serious adverse events(SAEs) related to the study drug is more than 2, and the proportion exceeds 20% of the number of enrolled people in this arm; 2) More than 1 case of liver failure or death related to the study drug and the proportion exceeds 10% of the enrolled population in this arm; 3) Other situations require discontinuation of arm decided by the Safety Reviewer Committee (SRC).

Stage 2, equivalent to a phase III trial, will expand subsequent enrollment, if the safety evaluation in stage 1 meets all the following three conditions:1) The arm has not stopped in advance due to safety; 2) The trial has been assessed as tolerable (defined as the upper bound of the 90% one-sided confidence interval of the percentage of participants permanently discontinuing treatment < 30%); 3) There is no other situation that warrants discontinuation of the study arm after the decision by the SRC.

### Patient eligibility criteria

In addition to volunteering to participate in this clinical trial, the main eligibility criterion is pulmonary TB caused by *Mycobacterium tuberculosis* susceptible to rifampicin detected by molecular or phenotypic susceptibility testing. Participants must have a respiratory specimen, that is either positive for acid-fast bacilli on smear microscopy or positive for *Mycobacterium tuberculosis* by Xpert® MTB/RIF (Cepheid, Sunnyvale, CA, USA). Besides, patients aged between 18 to 60 years and weighed between 40 to 80 kg are eligible for the trial. An individual meeting any of the following exclusion criteria will be excluded from screening: resistance to isoniazid, pyrazinamide, ethambutol, or fluoroquinolones, and patients with extrapulmonary TB or with an extensive lesion (extent of disease greater than 50% or the aggregate diameter of all lung cavities greater than 6 cm). In addition, considering the safety of the regimen, patients will be excluded if they suffer from impaired liver function, their estimated glomerular filtration rate is smaller than 90 mL/min/1.73m^2^, or live with human immunodeficiency virus (HIV). Patients will also be excluded if they are taking drugs that affected the efficacy or contraindications with this study drugs. Moreover, pregnant or breastfeeding women are excluded. Detailed inclusion and exclusion criteria are shown in Table 2.

**Table 2 Tab2:** ORIENT inclusion and exclusion criteria

